### **Interim analysis**

After 5 and 10 administrations and also at 48 weeks, patients will be tested by PCR to quantify HBV DNA in serum as well as for HBsAg and HBeAg seroconversion. A comparative study will be conducted for the same variables for internal comparisons between both groups in order to have a reference to standard treatment with a recognized efficacy.

a) A 20% superior percentage of viral load reduction to undetectable levels in the group treated with NASVAC compared to PegIFN treated group in any of the virological study cuts will be considered as a success criteria for the Interim Analysis.

b) A superior difference in the proportion of patients with ALT normalization or combined ALT normalization and viral load reduction to undetectable levels at a defined time (5, 10 dosis or 48 weeks) between groups will be considered a success criteria for the Interim Analysis.

e) A sustained biochemical (ALT) response during three consecutive determinations after dose number 10 will be considered a success criteria.

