### **Design of the trial**

The population sample to be tested will be of 160 CHB patients, with variable serum transaminase levels, without treatment for at least 6 months, selected according to inclusion and exclusion criteria and allocated in two study groups (SG). The first study group, SG1 will include 80 CHB patients (HBeAg (+) and HBeAg (-)) that will be treated with 1 mL NASVAC (100 mcg per antigen, per dose per patient), administered in two cycles of inoculations, the first one by the intranasal route with five intranasal inoculations every 14 days each. During the second cycle patients will receive the same dosis (100 mcg per antigen) by the intranasal route and additionally the same dosis by the SC route,

The SG2 will be treated with Alpha-Interferon at standard dosis (weekly injection by SC route).

The treatment is discontinued for all patients of SG1 after completion of both cycles. The evaluation will continue during one year, but an interim report will be released after 5 and 10 administrations.

During the whole treatment period up to one year from the beginning of treatment, the systematic assessment of patients is launched to determine to what extent the treatment has driven them to generate the capacity to control the HBV load. This information is included in Figure 1.

[figure not shown]

**Figure 1.** General Algorithm of the trial

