### Treatment schedule

The NASVAC TVC will be administered **to SG1** during the first cycle in a final volume of 1.0 mL (100µg of HBsAg and 100µg of HBcAg) by intranasal route with 8 actuations of 125 µL until completing . The second cycle will continue the IN administration in the same dosis and frequency and simultaneously the same treatment will be administered by the SC route. The device to be used (Valois VP7D spray pump) will be actuated with five minutes intervals between actuations in the same nostril.

The pegylated IFN will be administered **to SG2** weekly by subcutaneous route in the established dose (180µg) .

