## Evaluation of the viral infection markers and statistic hypothesis

**HBV-DNA:** Response: Undetectability of HBV DNA in the serum of infected patient by using a quantitative PCR assay with 250 copies/mL as a viral detection limit of sensitivity at the end of therapy with NASVAC TVC as well as in every study cut starting from dose number five and ending at one year after treatment started.

The success criteria will be assessed one year after study started however it can be evaluated for Interim Analysis according to the date of virological assessment.

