## 12. Assurance

### Necessary resources

| Resources for 80 patients            | Amount per patient        | Total                        | Responsible                                                          |
|--------------------------------------|---------------------------|------------------------------|----------------------------------------------------------------------|
| NASVAC                               | 30 bb 500mL               | 3000 bb of NASVAC            | CIGB                                                                 |
| IFN alpha 2b                         | 48 bb
considering 48 w | 4 000 bb
considering 48 w | CIGB                                                                 |
| HBV DNA quantitative*                | 4                         | 700 tests                    | Labaid
Dhaka

and
Hospital and
Faculty of
Medicine |
| Anti-HCV, and anti-HIV*              | 2 (each)                  | 360 tests                    |                                                                      |
| Liver function and hematology tests* | 5 (each)                  | 900 test                     |                                                                      |
| ALT, AST*                            | 8 (each)                  | 1440 test                    |                                                                      |
| HBV serology *                       | 5 (each)                  | 900 test                     |                                                                      |

(\*) A number of tests will be used before definitive recruiting (before day 0).

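### Interim success over PegIFN can be declared after NASVAC dose 5 or 10, when the 48-week PegIFN course is only about 17–50% delivered

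*Protocol*

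**What the plan says.** **Cuts.** Under Interim analysis: "After 5 and 10 administrations and also at 48 weeks, patients will be tested by PCR".

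**Success rules.** Rule (a) concerns undetectable HBV DNA. A 20% advantage "compared to PegIFN treated group in any of the virological study cuts will be considered as a success criteria for the Interim Analysis". Rule (b) concerns ALT normalization, alone or combined with viral response. A difference "at a defined time (5, 10 dosis or 48 weeks) between groups will be considered a success criteria for the Interim Analysis". Neither rule is limited to a cut at which both courses have ended.

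**Main assessment.** The section on viral infection markers sets a later date but leaves the door open: "The success criteria will be assessed one year after study started however it can be evaluated for Interim Analysis". It also defines response at the end of NASVAC therapy and at each cut from the fifth dose, so the cuts run on the vaccine's clock.

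**NASVAC course.** Design of the trial gives two cycles, "the first one by the intranasal route with five intranasal inoculations every 14 days each". Treatment schedule adds: "The second cycle will continue the IN administration in the same dosis and frequency". The table of determinations puts the vaccine's end of treatment at week 24.

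**PegIFN course.** It is given weekly. The table puts its end of treatment at week 48, and Necessary resources budgets 48 vials per patient, "considering 48 w".

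**The concern.** The two courses differ in length by a factor of about two, and the early cuts are timed by the shorter one. Two of the three cuts therefore set a half or full vaccine course against an unfinished control course. If PegIFN response is still building, the observed difference at those cuts mixes efficacy with speed of completion, and the rule labels the result a success.

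This is bias, not chance. Putting both arms on common calendar weeks, or replacing the observed lead with a formal test, would leave it in place. At stake is an interim report that claims success over standard treatment on a lead that could shrink or vanish once PegIFN is finished. Design of the trial says such a report will be released after 5 and 10 administrations.

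**Working it through.** **1. Course lengths, checked against the protocol's supply figures**
- PegIFN: 1 injection per week × 48 weeks = 48. This matches the 48 vials per patient.
- NASVAC: a 100 µg dose is two 0.5 mL vials. Cycle 1 is 5 × 2 = 10 vials. Cycle 2 is 5 × (2 intranasal + 2 subcutaneous) = 20. The total is 30, which matches the 30 vials per patient.

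This confirms a 10-administration vaccine course and a 48-injection control course.

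**2. Share of the PegIFN course delivered at each cut (weeks elapsed / 48)**

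With dose 1 at week 0 and 14-day intervals, dose 5 falls at week 8. Dose 10 falls at week 18 if there is no gap between cycles. The gap is not stated, so the tabulated visits (weeks 12 and 24) give the upper ends.

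| Cut | Timing | PegIFN delivered |
|---|---|---|
| Dose 5 | week 8 / 10 / 12 | 17% / 21% / 25% |
| Dose 10 | week 18 / 20 / 24 | 38% / 42% / 50% |
| Week 48 | week 48 | 100% |

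At dose 5 NASVAC is 5/10 = 50% given by administrations, but 10/30 = 33% by vials.

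**3. What the rule would do if the treatments were equally effective in the end**

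Let r be the common eventual response, and let f_N and f_I be the fractions of it reached at the cut by NASVAC and PegIFN. With n per arm, X_N ~ Bin(n, f_N·r) and X_I ~ Bin(n, f_I·r). The quantity is P[(X_N − X_I)/n ≥ 0.20], computed exactly for a single cut.

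Inputs:
- r = 30% is the figure the background section gives for current treatments, on unspecified criteria.
- r = 50% is the uncontrolled NASVAC month-12 result in the clinical experience section.
- Both rates are assumptions here, as are all values of f.
- n = 80 follows Design of the trial (160 in total, 80 in the first group). The Number of patients section says 60 per group, so that is shown too.

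| f_N | f_I | n=80, r=30% | n=80, r=50% | n=60, r=30% | n=60, r=50% |
|---|---|---|---|---|---|
| 100% | 100% | 0.4% | 0.7% | 1.1% | 1.8% |
| 100% | 75% | 4% | 19% | 7% | 23% |
| 100% | 50% | 25% | 78% | 29% | 75% |
| 75% | 50% | 2.7% | 17% | 5% | 21% |
| 50% | 50% | 0.03% | 0.2% | 0.2% | 0.8% |

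The inflation comes from the gap between f_N and f_I. It is small when PegIFN is near its final response, and it disappears when both arms are equally far along.

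**The case against.** **Interim only.** A reader might infer that the trial could reach its final superiority conclusion on early data. The documents do not support that. The main success assessment is at one year, after PegIFN ends at week 48. The interim section describes the group comparison as internal and as a reference to standard treatment. Nothing ties interim success to stopping the trial, dropping the control or a final claim. This limits the harm to the interim statement. It does not remove it, because the same section that fixes one year also permits interim use.

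**How little PegIFN has been given.** A reader might put it at 10% at dose 5, from 5/48. That requires each arm to count its own injections, whereas the protocol ties the cuts to NASVAC doses and uses one calendar table for both arms. The supported lower end is 17%.

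**One-sided illustration.** Setting the vaccine at full response while scaling down PegIFN favours the concern, most of all at dose 5. In the pilot, 6 of 13 HBeAg-negative patients were undetectable after five doses and 8 of 13 at month 12, so 6/8 = 75% of the later figure had been reached. With the vaccine at 75% and PegIFN at 50%, the chance falls from 25% to 2.7% (r = 30%) and from 78% to 17% (r = 50%). This stands, and no single probability should be quoted as the size of the problem.

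**The hypothesis.** A reader might say that the early cuts contradict the stated hypothesis, which concerns response once treatment is complete. That phrase can be read as completion of NASVAC alone, in which case the dose-10 cut fits it. The point does not rest on this reading.

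**Week 48 is not symmetric either.** PegIFN is then at end of treatment and NASVAC about 48 − 24 = 24 weeks past it. True, but both courses are complete.

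**Conclusion.** The point holds in a limited form. Rules (a) and (b) allow interim success at two cuts where PegIFN is about 17–25% and 38–50% delivered, so such a success need not mean superiority over a completed PegIFN course. That part rests on the protocol's text and schedule alone.

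The size is not known. It depends on how fast response builds in each arm, which the protocol does not give. Under equal eventual response of 30–50% and 80 per arm, the chance of an observed 20-point lead at one cut runs from under 1% (both arms at full response, or both at half) to 25–78% (vaccine at full response, PegIFN at half). Intermediate cases give 3–19%. If PegIFN is close to its final response by week 24, the bias at dose 10 is small.

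The one-year assessment is untouched. The defect is a success label that the early cuts cannot support, and it is cheap to remove.

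**What to change.** 1. In Interim analysis, rules (a) and (b), state that the dose-5 and dose-10 comparisons with PegIFN are descriptive, on-treatment results and not success criteria. This fits the section's own stated purpose of internal reference.
2. Allow success over PegIFN only at a cut where both planned courses are complete: week 48, the one-year assessment, or later. Note there that at week 48 NASVAC patients are about 24 weeks off treatment.
3. Change the matching interim wording in the section on viral infection markers at the same time. Otherwise it would still permit the success criterion at the early cuts.

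**Cost.** No added patients, visits or tests, and no change to treatment. The sponsor gives up an early success claim. The General schedule starts recruitment in October 2010 and places the interim in May–June 2011, at most about 39 weeks later. On those dates no patient could have reached week 48, so that interim becomes descriptive as regards rules (a) and (b).

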### **General schedule**

| Period                                  | Beginning | Termination |
|------------------------------------------------|------------------|--------------------|
| Preparation of the protocol and its amendments | Sep / 2009       | Oct / 09           |
| Recruitment and treatment of patients          | Oct / 2010       | Jun / 2011         |
| Management and processing of data              | Oct / 2010       | Dec / 2012         |
| Interim analysis                               | May / 2011       | Jun / 2011         |
| Final analysis                                 | Dec / 2012       | March / 2013       |

*Flexibility will be accepted in schedule on the basis of recommendation of Principal investigator.*

## **11. Practicalities**

### **Detailed plan. Subject management**

Patients from the Gastroenterology outpatient consultation potentially can participate in the protocol. These sessions should take place at least once per week and the following steps will be taken with every patient that fulfills the inclusion criteria:

- Clinical examination by specialists.
- Laboratory analyses
- If the patient fulfills the rest of the inclusion criteria and does not have any of the exclusion criteria, his written consent is requested after the proper explanation.
- The individual data form will be filled.
- The patient will receive an explanation about the treatment and its time of duration.
- The day before the beginning of treatment, serum samples will be taken for the baseline data.
- The injections will take place every fortnight at the clinic. Clinical examinations will be done according to the established schedule.
- At each evaluative consultation the appointment for the next one will be established.

For the purpose of quantitative HBV-DNA determinations, the serum samples will be taken at the consultations and kept frozen until their transportation to laboratory. HBV-DNA determination for inclusion will be the same method to the one to be used during assay.

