### 5.4 Exclusion criteria

- Condition of asymptomatic HBV carrier, cirrhotic or primary hepato-cellular carcinoma patients
- Positive serological markers for hepatitis C or hepatitis delta virus.
- Positive serological markers for HIV
- Previous specific anti-hepatitis treatment in the last 6 months.
- Critically ill patient, heart or renal failure, hypertension, hyperthyroidism, epilepsy, immunodeficiency diseases, malignancies or any non-controlled systemic disease.
- Pregnancy or nursing women. Women in fertile ages without any contraceptive methods.
- Known severe allergic conditions (degree III or IV asthma, urticaria, dermatitis, bronchitis, etc. or hypersensitivity to any of the ingredients present in the preparation such as thiomersal.
- Severe psychiatric dysfunction or another limitation that prevents the patient's consent.
- Autoimmune diseases (such as lupus, rheumatoid arthritis, multiple sclerosis, non controlled diabetes mellitus type 1)

- Other hepatic diseases of different etiology (such as alcoholism, auto immune hepatitis, toxic hepatitis, Wilson diseases, hemochromatosis)
- Treatment with immune suppressive disorder or administration of immune suppressive-immune modulator drugs (including steroids) during or in the 6 months previous to the study.
- Very high transaminase levels at the beginning of treatment (ALT over 500 U/L) suggesting a not stable disease with risk for patient's health or acute flares over 15 times the upper limit of normality.

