### **Quality control and audits**

Monitoring will be done at regular intervals, depending on the progress of the investigation. The objective of the control is to check compliance with Good Clinical Practices (GCP) guidelines, demanded by sponsor. These visits will be serving to discuss any aspect of the protocol that the investigator suggests.

The investigator and the hospital unit where he belongs will permit that the monitors (properly authorized by CIGB / Labaid Dhaka hospital) audit and review the documents of the investigation and the use of the given resources. The Case Report Form models of patients will be verified, which permits a comparison with the original clinical histories.

An initiation visit will be carried out. It is foreseen to carry out monitoring and control of the quality visits to each investigation place.

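### Written consent is requested only after laboratory tests and a completed eligibility check, so tests done solely for the trial can precede consent

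*Protocol*

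**What the plan says.** All references are to the Protocol.

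- **Section 11, Detailed plan. Subject management.** The list opens with "Clinical examination by specialists", followed by laboratory analyses. The third item is: "If the patient fulfills the rest of the inclusion criteria and does not have any of the exclusion criteria, his written consent is requested". The data form, an explanation of the treatment and its duration, and the baseline serum sample on the day before treatment come after that. The same section adds: "HBV-DNA determination for inclusion will be the same method to the one to be used during assay".
- **Section 5.4, Exclusion criteria.** The list includes "Positive serological markers for HIV" and "Positive serological markers for hepatitis C or hepatitis delta virus".
- **Section 5.3, Inclusion criteria.** HBV DNA thresholds are set separately for HBeAg-negative and HBeAg-positive patients. Signed consent is itself one of the inclusion criteria.
- **Section 12, Necessary resources.** The starred rows include quantitative HBV DNA and "Anti-HCV, and anti-HIV". The footnote to the star reads: "A number of tests will be used before definitive recruiting (before day 0".
- **Section 9, Procedures (forms table).** The consent form is to be completed ahead of each patient's inclusion. Screening is not mentioned.
- **Section 3, General ethical considerations.** Written consent follows proper information, and the patient may refuse at any moment without effect on care. No timing relative to screening tests is given.
- **Section 11, Quality control and audits.** Monitoring is to "check compliance with Good Clinical Practices (GCP) guidelines".

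**The concern.** Consent should authorise what is done to a patient for the sake of a trial. Here the request for consent depends on results that have to exist already. If some of those results come from tests ordered only to decide trial eligibility, the patient has been tested for the trial before agreeing to it. A patient found ineligible then drops out of the sequence before the consent step and may never be asked. HIV serology makes this more than a formality, because a positive result has consequences for the patient well beyond the trial.

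This is an operational rule that sites will follow step by step, so it is not a detail that a statistical analysis plan would settle.

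**Working it through.** No sample size, power or error rate is involved. The check is whether the order of steps forces tests ahead of consent, and whether any other section corrects that.

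1. **Is the order real, or only an accident of the bullets?** The consent item is conditional: it applies if the remaining inclusion criteria are met and no exclusion criterion is present. Because signed consent is one of the inclusion criteria in section 5.3, the reference to the rest of them means that every other criterion has been settled first. The condition itself fixes the order: examination, laboratory analyses, eligibility check, consent.

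2. **Which results does the check need?** Ruling out the exclusions in section 5.4 needs HIV, hepatitis C and delta serology. Meeting section 5.3 needs HBeAg status and an HBV DNA value.

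3. **Are any of these tests done for the trial rather than for routine care?** Section 11 says the HBV DNA result used for inclusion comes from the same method as the later trial determinations. The resources table in section 12 lists quantitative HBV DNA, anti-HCV and anti-HIV as resources for the trial. Delta serology is not named in that table. The footnote says that some of the starred tests are used before recruitment. No section describes HIV serology, or HBV DNA by the trial's method, as routine care.

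4. **Does another section put consent earlier?**

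| Place | What it says on the timing of consent |
|---|---|
| Section 3, general ethical considerations | After information; nothing about screening tests |
| Section 3, how patients are informed | Free decision and written consent; nothing about screening tests |
| Section 9, forms table | Ahead of inclusion |
| Section 11, step list | After the eligibility check |

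None of these moves consent ahead of the tests, and no separate screening consent is described. The entry in section 9 agrees with the order in section 11 and so does not repair it.

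5. **Which steps clearly follow consent?** Only those listed after it: the data form, the explanation of the treatment and its duration, the baseline serum sample and the treatment itself. The consent item does call for a proper explanation first, so placing a further explanation of the treatment after it should be tidied in the same edit.

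**The case against.** The strongest counter-argument is routine care. Patients come from a gastroenterology outpatient clinic with an established diagnosis. Section 5.2 already rests that diagnosis on more than 6 months of HBsAg, detectable HBV DNA by quantitative PCR, and an abnormal ALT value or a biopsy history. Much of the examination and laboratory work may therefore be ordinary care that needs no trial consent. This stands for HBsAg history and past ALT. It is not established for HIV serology or for HBV DNA by the trial's method, which the Protocol counts as trial tests and does not separate from routine ones.

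The resources footnote is also weaker than it looks. It names no test, and the period before day 0 includes the baseline serum sample, which follows consent. It fits testing before consent but does not prove it. The conditional consent step carries the point.

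A reader might infer four stronger things that the documents do not support:

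- **A reserve of tests for unconsented screening.** Taking 160 patients, 700 − 4 × 160 = 60 HBV DNA tests and 360 − 2 × 160 = 40 anti-HCV/anti-HIV tests appear spare. But 360 / 2 = 900 / 5 = 1440 / 8 = 180, which is the total given under Number of patients in section 10. At 180 patients the anti-HCV/anti-HIV requirement is exactly 360, and the HBV DNA requirement is 4 × 180 = 720, more than the 700 supplied. No reserve is shown, and a reserve would not reveal whether a test came before consent.
- **Results stored for patients never included.** The description of Annex 8 in section 9 covers who attended with the diagnosis and whether they were included. It mentions no test results.
- **A contradiction with section 3.** That section gives no timing, so the step list fails to secure its promise but does not contradict it.
- **Selective entry.** Eligibility data are normally known before enrolment even when consent comes first, so the order of consent does not create this risk.

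**Conclusion.** The point holds in a limited form and should be corrected. As written, section 11 makes consent conditional on an eligibility check that needs tests the Protocol itself counts as trial tests, and no other section places consent earlier. Tests done solely for the trial can therefore precede consent, and patients who fail screening may never be asked. This does not secure the informed, refusable participation promised in section 3, or the GCP compliance that section 11 names as the monitoring standard.

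The conclusion rests on two assumptions. First, HIV serology is among the early tests. This is inferred from the exclusion criterion, the conditional consent step and the resources table taken together; the step list does not name it. Second, at least some of the eligibility tests are not already available from routine care, which the Protocol does not say either way. The consent form was not available for this review.

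The number of patients affected cannot be derived from the documents. The matter concerns patient protection and has no effect on the primary comparison, the analysis or the sample size.

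**What to change.** - In section 11, Detailed plan. Subject management, move the explanation of the trial and the written consent ahead of any examination or laboratory test done solely for the trial. The explanation of the treatment and its duration should move with it.
- In the forms table of section 9, change the timing of the consent form to: before any trial-specific examination or test.
- State that results already obtained in routine care, such as HBsAg history and past ALT, may still be used for pre-screening.

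The cost is a reordering of steps, one table entry and one added sentence, plus more consent discussions with patients who later fail screening. No further test is needed.
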